### Intervention: palliative Care in day Hospital

In the course of a 2 to 4-hour stay in PCDH, patients and their families are cared for by the PC team composed of a doctor and a nurse, with a standardized procedure:
Assessment of palliative care needs, carried out by the palliative care team (30 to 60 min)Intervention of at least 2 supportive care professionals who can be psychologists or psychiatrists, social workers, physiotherapists, or dieticians (30 to 60 min)Intervention by an oncologist if needed, often in a joint meeting with the PC team (15 to 30 min)Complementary investigations if needed (biology, radiology, medical imaging)Technical care if needed (central venous catheters installation, transcutaneous electrical neuro-stimulation sessions, complex dressing of malignant wounds, pleural or ascites evacuating puncture.A specific time allocated to focus on patients’ needs for information, such as shared decision-making, the aims of anti-cancer treatment, the risk of complications, prognosis, and advance care planning (30 to 60 min)A specific time allocated for the PC team to liaise with the home health-care professionals (30 to 60 min)

The main characteristics of PC delivery in PCDH are summarised in Table 1.

**Table 1 Tab1:** Comparison of the conditions of care delivery between standard outpatient PC and PCDH

	Standard outpatient PC	PCDH
Symptom relief	- Advice and medication - Planning for additional tests and specialized consultations	- Advice and Medication - Planning for additional tests and specialized consultations - Immediate titration or imaging if needed - Supportive care team intervention - Pleural or ascites evacuation
Relationship building and education	Consultation length < 30–45 min with the PC physician	- Consultation duration > 2 h with the PC team, physician and nurse - Dedicated time for relatives - Dedicated time for care coordination
Consultation and decision-making	PC physician for a short time	- Oncologist and PC physician - Longer time for discussion
Advance care planning	PC physician for a short time	- PC physician and nurse - Longer time for discussion

Abbreviations. *ME* Medical-Economic; *PC* Palliative Care; *PCDH* Palliative Care Day-Hospital

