### Medico-economic study

The study will be carried out from a societal point of view. A cost estimate will be made by collecting actual care consumption from the patients’ files for the last 3 months of life and assumptions will be made to estimate costs between inclusion in the study and the last 3 months of life.

Only costs that discriminate between the two strategies will be taken into account. Direct medical costs are costs directly attributable to the pathology and/or its treatment: care and medical and social expenditure.

These costs will include:

- Consultations carried out by community health (source of price data: fees established in General classification system for the professional activities, NGAP);

- Expensive medical and technical procedures such as MRI, or scanners (source of price data: fees established in the Common Classification of Medical Acts, CCAM);

- Hospitalization at home (source of price data: National average DRG related stay cost, ENCC 2016);

- The professionals’ interventions from the palliative care network or the mobile palliative care team (source of price data: bundled payment received by Hospital for public missions, MIGAC);

- Hospitalization in health care institutions, including rehabilitation units, acute medical care, etc. (source of price data: bundled payment received by Hospital for public missions, MIGAC);

- Care in day hospitalization (source of price data: National Cost Study 2016);

- Consultations in medical emergencies (source: of price data National average DRG related stay cost, ENCC 2016);

- Consumption of chemotherapy or other anti-cancer treatment (source of price data: Drug tariff database, BDM-IT);

- Medical transport expenses (source of price data: tariff established by the National Health insurance; the use of non-medicalized and non-healthy transport will be valued according to the rate per kilometer of transport and the distances travelled per kilometer).

A cost-effectiveness analysis will be conducted using the Global Survival effectiveness criteria.

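### Emergency consultations are priced from a hospital-stay cost, so the cost comparison between the arms may be biased

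*Protocol article*

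**What the plan says.** The Medico-economic study section of the protocol article lists the cost items with a price source for each. The lines that matter here are:

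- Emergency visits: "Consultations in medical emergencies (source: of price data National average DRG related stay cost, ENCC 2016".
- Home hospitalization, from the same source: "Hospitalization at home (source of price data: National average DRG related stay cost, ENCC 2016".
- Institutional hospitalization, as a separate item: "Hospitalization in health care institutions, including rehabilitation units, acute medical care, etc. (source of price data: bundled payment received by Hospital for public missions, MIGAC".
- Day hospital: "Care in day hospitalization (source of price data: National Cost Study 2016".
- Imaging and technical acts: "Expensive medical and technical procedures such as MRI, or scanners (source of price data: fees established in the Common Classification of Medical Acts, CCAM".

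The same section takes actual consumption from patient files for the last three months of life. Under Endpoints, emergency consultations and hospitalizations appear as distinct events among the end-of-life aggressiveness criteria. Under Objectives, the trial aims to lower both that aggressiveness and the cost of care over those same three months.

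**The concern.** The event counted is a consultation, but the price attached to it is described as the average cost of a stay. If a stay costs more than a visit, every emergency visit without admission is overpriced. Where a visit ends in admission, the hospitalization line also applies, and the article gives no rule to stop both being charged for one episode.

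The error falls on an item expected to differ between arms. If PCDH works as intended, it reduces emergency use, and each avoided visit is then credited at the wrong price. The result feeds a stated secondary objective and the planned cost-effectiveness and cost-utility analyses. The Discussion says that positive trial results could lead to national guidance on setting up such units.

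**Working it through.** The article states no unit price, volume or cost difference, so there is no figure of its own to reproduce. The check is a comparison of its sections, followed by the algebra of the bias and an illustration on assumed values.

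**1. Unit of the event against unit of the price.** Endpoints separates emergency consultations from hospitalizations, and the cost list gives each its own line. The emergency line nevertheless carries the same stay-based source label as home hospitalization. On the article's own wording, the price unit does not match the event.

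**2. Bias for visits without admission.** Let *s* be the price applied, *v* the proper cost of a visit, and Δ the mean number of such visits per patient in PCDH minus control.

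- Error per visit = *s* − *v*.
- Bias in the incremental cost of PCDH = Δ × (*s* − *v*).
- The bias is zero if Δ = 0 or *s* = *v*. It is negative, making PCDH look cheaper, if Δ < 0 and *s* > *v*.

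**3. Visits that lead to admission.** If the admission price already covers the emergency episode, the correct extra charge is zero. Charging *s* as well then adds a bias of Δa × *s*, where Δa is the arm difference in such visits. The article does not say what the admission price covers or whether these visits are charged separately, so this is a possibility only.

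**4. Illustration, all values assumed.** Take one day-hospital stay as 1 unit. Assume six PCDH sessions per patient, an outpatient consultation *c* of 0.1 to 0.2, a proper emergency visit of 0.3, overpricing of 0.5 to 1.0 per visit, and Δ from −0.5 to +0.5. Correct incremental cost = 6 × (1 − *c*) + Δ × 0.3. With *c* = 0.2 and overpricing of 1.0:

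- Δ = −0.5: 4.80 − 0.15 = 4.65; bias −0.50; −0.50 / 4.65 = −10.8%.
- Δ = 0: bias 0.
- Δ = +0.5: 4.80 + 0.15 = 4.95; bias +0.50; +0.50 / 4.95 = +10.1%.
- Three sessions instead of six, Δ = −0.5: 2.40 − 0.15 = 2.25; −0.50 / 2.25 = −22.2%.

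The last line shows how far the percentage depends on what is assumed.

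**5. Imaging.** The Intervention section allows "Complementary investigations if needed (biology, radiology, medical imaging" within a PCDH stay, and its Table 1 lists "Immediate titration or imaging if needed". The cost list has separate lines for day hospital and for imaging. It does not say what the day-hospital cost contains, or whether procedure fees apply to scans done during a costed stay. The Procedure section allows hospitalization in both groups, so control imaging can also fall within a costed stay.

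**6. Price year.** The year 2016 appears on the home hospitalization, day-hospital and emergency lines. The other sources carry no year, and the trial was registered in October 2020. At an assumed 0 to 3% a year over four to six years, the drift runs from 0 to 1.03^6 − 1 = 19.4%.

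**The case against.** The strongest defence is that the stay-cost wording is only the article's generic name for a cost database. It is used for home hospitalization too, and the database may hold a proper per-visit emergency cost. That depends on a source not shown. If it is true, *s* = *v* and the bias disappears, but the text as written still directs the analyst to a stay cost. This is a stated rule, not a detail left to a fuller document.

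Double counting of admissions is inferred, since nothing says that such visits will be charged on top of the stay. The hospitalization line is itself priced from a bundled payment for public missions, which on its wording is not a per-stay price. This objection stands, and the most that can be said is that part of an admission may be counted twice.

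A reader might also infer that imaging is counted twice in the experimental arm. The documents do not support that. It assumes that the day-hospital cost includes scans and that procedure fees will be added for them, and neither is stated. In-session imaging is conditional on need, experimental patients without an indication for PCDH receive an outpatient consultation instead, and control imaging may also occur during a stay.

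A reader might likewise infer that the stay-based items as a class are fixed at 2016 prices. Institutional hospitalization is stay-based and undated, and nothing says the 2016 values will not be updated. A condensed article commonly leaves the common price year to the full plan.

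**Conclusion.** The point holds for emergency visits. The article fixes a price source whose stated unit is a stay for an event that is a consultation, on an item that may differ by arm. The incremental cost of PCDH may therefore be biased, in favour of PCDH if PCDH reduces emergency visits and a stay costs more than a visit.

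It would go too far to say that the incremental cost is distorted, or that its sign turns on these rules. No price or volume is given, the size cannot be derived, and the percentages above only illustrate assumed values. Any duplicated imaging in PCDH would push against PCDH, so the net direction of all the costing questions together is also open.

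Imaging and price year are minor clarifications. The consequence is limited to the economic analyses, and the primary quality-of-life analysis is not touched.

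**What to change.** - Price emergency visits without admission from a per-visit cost or tariff, and name the source.
- Do not cost separately an emergency visit that leads to a costed admission. State the unit of the institutional hospitalization price at the same time, because this rule relies on it covering the admission.
- As clarifications, confirm in either arm that no procedure fee is added for imaging already included in a costed stay, and express all unit costs in one stated price year.

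The cost is a rewording of the unit-cost list, one indicator per emergency visit (admitted or not) and one per procedure (inside or outside a costed stay). Consumption is already taken from patient files, so no new patient contact should be needed.

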## Discussion

Several PC types of structure are usually described for integrated PC in oncology: inpatient consultation, outpatient clinics, palliative care units, community-based palliative care and hospice care (30). In a survey from 184 ESMO designated cancer centers of integrated PC there were present at 90, 89, 71 and 50% respectively [51]. In this survey 70% of patients with advanced cancer had a PC consultation before death, occurring 90 days before death for outpatients and 21 days for inpatients and 118 (78%) reported that routine symptom screening was offered in the oncology. Outpatient PC can facilitate timely referral but the optimal model of outpatient palliative care is not known. There are currently many variations for how PC is delivered in the outpatient setting, which can be described with some key characteristics: type of specialized PC staff (physician and/or nurse), team makeup (with or without psychologist, chaplain and social worker), place of in intervention (in oncology clinics or in stand-alone clinics), variously embedded joined PC and oncology staff during consultation, mixed PC and oncology meetings or other modalities of education [52, 53]. The effect of an embedded advanced practice PC nurse has been assessed only with non-randomized studies and small sample size, and the heterogeneity of the models of PC delivery made analysis difficult [54, 55]. In the same way, the effect of an embedded PC team with a physician and a nurse was assessed with a pre/post study design [56–58]. At this time, interdisciplinary specialist PC in stand-alone clinics remains the gold standard for ambulatory palliative care because this approach has the greatest impact on multiple patient and caregiver outcomes [52]. Regarding the particularly promising conditions for PC delivery in these structures, PCDH could be the optimal place for outpatient palliative care. One of the strengths of PCDH is the interdisciplinary PC approach aiming to provide symptoms relief, psychosocial support, education and shared decision making, responsibility and advance care planning. The physician, nurse, psychologist, social worker, chaplain, pharmacist, physiotherapist, occupational therapist, and other allied health professionals each contribute their unique expertise while working together in a cohesive manner to support the patient’s goals of care through impeccable assessments, coordinated communication, and multidimensional interventions. Not all members are required at all times, some may be needed more often than others, and some may form a closer relationship with the patient. Moreover, PCDH setting to deliver integrated PC promote concertation between oncologists, PC with or without patients and relatives, and care coordination with home health caregivers. Progress in cancer therapy over the past two decades, particularly in targeted therapies or immunotherapy, has focused on extending the life expectancy of metastatic patients with incurable metastatic disease rather than on the rates of cure [59]. As integrated PC is a gold standard of care, this has led to a considerable increase in the need for outpatient palliative care facilities in cancer centres [12]. In addition, hospitalization in oncology is proving more and more difficult in some places. Consequently, if the results of our trials confirm the major role of PCDH in outpatient PC delivering, this could lead to national guidelines to develop these structures in all comprehensive cancer centres.

To the best of our knowledge, this is the first randomized controlled trial to set out to compare PCDH with usual palliative care. This study will broaden perspectives in ambulatory palliative care and will promote PCDH as a new palliative care setting. Randomisation will give a strong weight to eventually positive results. Problems associated with conducting RCT in PC are well documented. Despite these difficulties, the improvement of evidence base of PC is essential and RCTs are a recognized method to provide these proofs [60, 61]. Another strength of this project is its design with a mixed-method: a randomised clinical trial testing the hypothesis of an impact of the PCDH on HRQoL and a qualitative study understanding PC organization and exploring factors that could promote or impede the efficacy of specific palliative care facilities in a hospital cancer unit. Indeed, mixed-methods research is becoming an important methodology to investigate complex health-related topics and gain a more complete understanding of systems in health [62]. In a context of the control of medical health expenditure, the biggest challenge is to find the right combination in order to improve quality of care and both control structural costs. The medical and economic study in our trial will contribute to the assessment of the effectiveness and economic consequences of PCDH compared to PC ambulatory consultations. Therefore, our study will broad the ambulatory palliative care perspectives and will promote the PCDH as a new PC outpatient setting.

## Data Availability

Not applicable.

## Abbreviations

ASCO: American society of clinical oncology
ECOG: East cooperative oncology group
EOL: End-of-life
EORTC QLQ-C30: European Organization for research and treatment of cancer quality of life questionnaire core30
EQ 5 D: EuroQol 5 dimensions
HADS: Hospital anxiety and depression scale
HRQOL: Health-related quality of life
ICECAP-SCM: Index of capability supportive care measure scale
Out-PATSAT7: Out-patient satisfaction 7
Out-PATSAT-C33: Out-patient satisfaction Core33
PC: Palliative care
PCDH: Palliative care day-hospital
PTPQ: Prognosis and treatment perception questionnaire
QFS: Quality of life survival deterioration free survival
RCT: Randomized controlled trial
SCNS-P&C-F: Supportive care needs survey for partners and caregivers French version
